## Abstract

**Background:**

With the development of computed tomography (CT) technology, coronary CT angiography can be acquired with low doses of radiation and contrast agent without a loss of diagnostic performance. The primary objective of the CONCENTRATE study is to prove the noninferiority of the enhancement effect of low-concentration contrast agents compared to a high-concentration contrast agent of the coronary artery and myocardium with coronary CT angiography.

**Methods/Design:**

The CONCENTRATE study is a prospective, multicenter, noninferiority, randomized trial evaluating the enhancement effect of low-concentration contrast agents (270 and 320 mg iodine/ml) compared with a high-concentration contrast agent (370 mg iodine/ml) in the coronary artery and myocardium of coronary artery CT angiography. The primary efficacy measurement is the enhancement of coronary arteries as measured in Hounsfield units. The target population comprises 318 patients with suspected coronary artery disease who have been referred for clinically indicated nonemergent coronary CT angiography. Eligible participants are randomized for three different concentrations of the contrast agent in a 1:1:1 allocation ratio to one of three arms. The CONCENTRATE trial is a double-blind study, where the subjects and the outcome assessor are blinded to the concentration of the contrast agent used for coronary the CT angiography. Eight clinical sites in Korea are participating in this trial.

**Discussion:**

The CONCENTRATE study will determine whether low-concentration contrast agents are able to provide diagnostic image quality in coronary CT angiography.

**Trial registration:**

NCT02549794. Registered on 14 September 2015.

**Electronic supplementary material:**

The online version of this article (doi:10.1186/s13063-016-1441-y) contains supplementary material, which is available to authorized users.

## Background

Due to developments in computed tomography (CT) technology, cardiac CT has become very useful as a noninvasive examination technique in the diagnosis of obstructive coronary artery disease (CAD), and the accuracy has increased to more than 90 % [1–5]. Specifically, cardiac CT plays a gatekeeper role in reducing invasive cardiac angiography implemented solely for the purpose of diagnosis [6]. However, cardiac CT also has disadvantages, particularly the exposure of patients to radiation and iodine contrast agent. Consequently, considerable effort has been devoted to identifying ways to reduce the radiation exposure and the amount of contrast agent used. A recently introduced method uses a combination of a scan with a low tube-based potential and iterative image reconstruction to reduce both the radiation dose and the amount of contrast agent used for coronary CT angiography [7]. According to recent studies of values from this combined method, the signal-to-noise ratio (SNR) and contrast-to-noise ratio (CNR), which represent image quality, are higher compared to the standard method [8, 9]. The standard method utilizes a scan with higher tube potential according to patient body mass index (BMI) and image reconstruction by makeshift filtered-back projection under conditions using the same amount of contrast agent. Therefore, the amount of contrast agent can be reduced while achieving the same contrast effect due to the advantage of the increased effect of contrast enhancement provided by the low tube potential. Therefore, efficacy studies using low-concentration contrast agents along with low tube potential are being performed [10].

The CONCENTRATE study intends to prove that, compared to the combined method using the makeshift filtered-back projection image reconstruction and standard image acquisition according to BMI and with a standard high-concentration contrast agent, the image quality does not deteriorate as a result of the combination of a scan with low tube potential and the iterative image reconstruction method with low-concentration contrast agents.

### Study objectives

#### Primary objective

The primary objective of the CONCENTRATE study is to determine the noninferiority of the contrast enhancement of cardiac CT with low-concentration contrast agents compared to that with high-concentration contrast agent.

#### Secondary objective

The secondary objective of the CONCENTRATE study is to determine the diagnostic accuracy of coronary CT angiography in the identification of anatomically obstructive CAD with low-concentration contrast agent compared with invasive coronary angiography (ICA) as the reference standard and to compare it to the accuracy achieved with a high-concentration contrast agent.

### Primary hypothesis

We hypothesized that the use of low-concentration contrast agent for coronary CT angiography and myocardial perfusion would not be inferior to the use of a high-concentration contrast agent in the enhancement effect in the coronary artery and in the myocardium.

## Methods/Design

### Trial design

The CONCENTRATE study is a prospective, multicenter, noninferiority, randomized trial evaluating the enhancement effect of low-concentration contrast agents consisting of 270 and 320 mg iodine/ml (mgI/ml), compared with a high-concentration contrast agent that contains 370 mgI/ml in the coronary artery and myocardium in coronary artery CT angiography. The target population includes patients with suspected CAD who have been referred for clinically indicated nonemergent ICA. Eligible participants are randomized for three different contrast agent concentrations in a 1:1:1 allocation ratio to one of three arms of the trial. The CONCENTRATE trial is a double-blind study, where the subjects and the outcome assessor are blinded to the concentration of the contrast agent used for coronary CT angiography. Eight clinical sites in Korea are participating in this trial. Every clinical site requires the approval of the site’s Institutional Review Board. The study protocol and the informed consent form should be approved by the Institutional Review Board at each participating site. A list of the Institutional Review Boards and the status of their respective approvals are provided in an additional file (see Additional file 1). Standard protocol items and organizational structures are provided as additional files (see Additional files 2 and 3, respectively). A flow chart of the study is provided in Fig. 1. The informed consent will be obtained from all participants (see Additional file 4).

**Fig. 1 Fig1:**
[figure not shown]
CONCENTRATE study workflow. CT, computed tomography; CAD, coronary artery disease

### Participants

Suitable participants include patients ≥ 20 years of age who have requested coronary CT angiography to assess clinical disease. The exclusion criteria include the following: 1) subjects suspected of having myocardial infarction, unstable angina pectoris, or coronary artery disease; 2) subjects with heart attack within 40 days prior to the CT scan; 3) subjects with a diagnosed complicated heart anomaly; 4) BMI > 35 kg/m^2^; 5) serum creatinine ≥ 1.5 mg/dl of renal insufficiency; 6) pregnant subjects; 6) subjects with a history of hypersensitivity reactions to contrast agents; 7) subjects with contraindications to the use of nitroglycerine; 8) subjects who plan to participate or enroll in other randomized clinical trials for cardiovascular disease; or 9) subjects with contraindications to the use of adenosine (e.g., bronchial asthma, 2–3 degree atrioventricular block, sick sinus syndrome, systolic blood pressure (SBP) less than 90 mmHg, recent prescribed history of dipyridamole, or hypersensitivity to adenosine) (Table 1). Patients who meet the selection criteria are registered by acquiring informed consent at the time an examination is ordered and during outpatient treatment by the investigators. Time schedule, interventions, assessments, and visits for participants are provided in a table (Table 2).

**Table 1 Tab1:** Inclusion and exclusion criteria

Inclusion criteria • Adults at least 20 years old • Subject who requested a coronary CT angiography to assess clinical disease Exclusion criteria • Subjects suspected of having myocardial infarction, unstable angina pectoris, or coronary artery disease • Subjects who experienced heart attack within 40 days prior to the CT scan • Subjects with a diagnosed complicated heart anomaly • BMI > 35 kg/m^2^ • Serum creatinine ≥ 1.5 mg/dl • Pregnant subjects • Subjects with a history of hypersensitivity reaction to contrast agents • Subjects with contraindications to the use of nitroglycerine • Subjects who plan to participate or enroll in other randomized clinical trials for cardiovascular disease. • Subjects with contraindications to the use of adenosine (e.g., bronchial asthma, 2–3 degree AV block, sick sinus syndrome, SBP less than 90 mmHg, recent prescribed history of dipyridamole, or hypersensitivity to adenosine)	

*CT* computed tomography, *BMI* body mass index, *SBP* systolic blood pressure

**Table 2 Tab2:** Schedule of forms and procedures

	Baseline	CT angiography	CT perfusion	Coronary angiography	Study evaluation
	Visit 1	Visit 2	Visit 3	Visit 4	
Screening	x				
Demographic	x				
Medical history	x				
Randomization	x				
Vital signs		x			
Laboratory test	x				
Vital signs 2		x			
CT angiography		x			
Vital signs 3			x		
CT perfusion			x		
Coronary angiography				x	
Study evaluation					x

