#### Myocardial perfusion CT

Stress myocardial perfusion CT will be performed in patients with at least one segment of greater than 50 % stenosis on coronary CT angiography. A static CT perfusion protocol will be used, and stress will be induced by infusing 140 mcg/kg/min adenosine under ECG monitoring for up to 6 min. The randomly assigned contrast agent, which was used for coronary CT angiography in the patient, will be injected 4 min 30 s after the adenosine injection, using the same injection method for contrast agent and image acquisition settings as used for the coronary CT angiography with the only difference being an additional scan delay of 2 s.

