## Abbreviations

AHA, American Heart Association; BMI, body mass index; CAD, coronary artery disease; CNR, contrast-to-noise ratio; CT, computed tomography; ECG, electrocardiography; HU, Hounsfield Unit; ICA, invasive coronary angiography; SNR, signal-to-noise ratio

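### Exclusion criterion 1 removes patients with suspected coronary artery disease, who are the stated target population, and the referral route is given in two conflicting ways

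*Protocol article*

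**What the plan says.** **Target population.** The Abstract (Methods/Design) describes "patients with suspected coronary artery disease who have been referred for clinically indicated nonemergent coronary CT angiography" and puts their number at 318. Trial design states: "The target population includes patients with suspected CAD who have been referred for clinically indicated nonemergent ICA".

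**Eligibility.** The Participants section takes in "patients ≥ 20 years of age who have requested coronary CT angiography to assess clinical disease". Its first exclusion is "subjects suspected of having myocardial infarction, unstable angina pectoris, or coronary artery disease". Table 1 repeats that exclusion in the same words.

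**Parts of the plan that need patients who may have CAD.** The Secondary objective is the accuracy of CT angiography for obstructive CAD "compared with invasive coronary angiography (ICA) as the reference standard". The Myocardial perfusion CT section says: "Stress myocardial perfusion CT will be performed in patients with at least one segment of greater than 50 % stenosis on coronary CT angiography". Secondary efficacy analysis plans sensitivity, specificity, predictive values and accuracy on a segment basis, with CAD defined as more than 50 % diameter stenosis.

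**The concern.** An exclusion criterion is an instruction to sites. This one, as worded, instructs them to turn away the patients whom the trial is meant to study. Eight sites are taking part. A site that follows the text literally enrols none of the intended patients. A site that does not must decide for itself what was meant, and the article gives it no guidance.

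The referral route matters for a different reason. Patients already referred for ICA and patients referred for CT angiography are likely to differ in their chance of having obstructive disease and in whether they go on to ICA. ICA is the reference standard for the secondary objective, so the route bears on who can contribute to the accuracy analysis and on the population to which its results apply.

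**Working it through.** No figure in the article bears on this point, so the check is a comparison of text.

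**Step 1: target population against exclusion 1.**

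| Place | Status of suspected CAD |
|---|---|
| Abstract, Methods/Design | Defines the target population |
| Trial design | Defines the target population |
| Participants, exclusion 1 | Excluded |
| Table 1, first exclusion | Excluded, same wording |

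The target population is a set of patients with suspected CAD. The eligible set contains only patients without suspected CAD. The two sets have no member in common, and this follows from the wording without any assumption. The exclusion stands in both the text and the table, so it is not a slip in one place.

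**Step 2: does another part of the article narrow exclusion 1?** The inclusion criterion speaks only of CT angiography requested to assess clinical disease, which does not say whether suspected CAD is in or out. Exclusion 2 deals separately with a heart attack in the 40 days before the scan and does not qualify exclusion 1. Listing CAD next to myocardial infarction and unstable angina may hint that acute or already established disease was meant, but no passage says so.

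**Step 3: which reading does the rest of the plan require?** Stress perfusion CT is triggered by stenosis above 50 % (Preparation of patients; Myocardial perfusion CT). Accuracy for obstructive CAD is the secondary objective. Data management foresees a repeat examination when image quality is too poor to settle whether there is significant CAD. All three presuppose enrolled patients in whom CAD is in question. The eligibility list is therefore at odds with the design as a whole.

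**Step 4: referral route.**

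| Place | Test for which the patient comes |
|---|---|
| Abstract, Methods/Design | Coronary CT angiography |
| Participants and Table 1, inclusion | Coronary CT angiography |
| Trial design | ICA |

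The Abbreviations list gives "ICA, invasive coronary angiography", so Trial design names a different test and is not using another term for the same one.

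**Step 5: what is not touched.** The primary measure is HU in the left main and proximal right coronary arteries, compared between randomized arms (Primary efficacy analysis). The Randomization section bases the 1:1:1 allocation on each site, so sites that interpret the criterion differently would not by that alone unbalance the arms. The sample size uses a margin, a standard deviation, alpha, power and a dropout rate. The eligibility wording is not among these inputs.

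**The case against.** **The literal reading is untenable.** Given the perfusion and accuracy components, sites would hardly read the criterion as barring everyone with suspected CAD. This is fair as a forecast: the contradiction does not show that the trial would enrol nobody, nor that the eight sites would in fact enrol different populations. It does not rescue the text. An eligibility rule that works only if sites disregard its wording is still wrong, and no passage supplies the intended meaning.

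**A reader might infer that the accuracy estimates are badly biased by selective verification.** The argument runs that patients come for CT, ICA then follows mainly positive scans, and sensitivity, specificity and negative predictive value are distorted. The Background lends some colour by describing cardiac CT as a gatekeeper to purely diagnostic invasive angiography. The documents do not support this as a finding:
- No passage makes ICA conditional on the CT result.
- Table 2 lists coronary angiography at Visit 4 without a condition. That does not prove ICA for everyone either, since the same table lists CT perfusion without a condition although the text makes it conditional.
- Fig. 1, the study workflow, is not shown.
- Under the route given in Trial design, patients are already referred for ICA and the problem largely disappears.
- Any size would rest on assumed verification rates. A patient-level calculation would also not carry over to the planned segment-basis analysis, because ICA in a CT-positive patient verifies that patient's CT-negative segments too.

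**A reader might also infer that the primary per-protocol set would be emptied**, because every target patient breaches exclusion 1. The article does not define that set or say that an eligibility breach leads to removal from it, so this remains conjecture.

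**Conclusion.** The inconsistency is established and the eligibility text is wrong as written. Exclusion 1, in both the Participants text and Table 1, excludes the population that the Abstract and Trial design define. On the literal reading, none of the target population is eligible. The referral route is contradictory between Trial design on one side and the Abstract and the inclusion criterion on the other. Both conclusions rest on the wording alone.

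The consequences concern who is eligible, how far the results generalize, and the secondary accuracy objective. Selective verification is a conditional note only: it arises if the route is CT referral and if ICA is then performed according to the CT result, and the article establishes neither. No size can be put on it from the documents.

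**What to change.** 1. Reword exclusion 1 in the Participants text and in Table 1 so that it agrees with the target population and no longer excludes suspected CAD. The sponsor should state which conditions the criterion is meant to cover; the documents do not show this.
2. Give one referral route in the Abstract, Trial design and Participants (with Table 1).
3. Only if that route is CT referral and ICA is done selectively by CT result: say so, and interpret or adjust the accuracy estimates for selective verification.

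Items 1 and 2 cost a short protocol amendment and a notice to the eight sites. Because recruitment began in July 2015, the notice should also ask each site how it has applied criterion 1 so far. Item 3, if it applies, adds some analysis code for a secondary objective. The randomization, primary endpoint and sample size need no change on this account.

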### Randomization

All enrolled subjects are randomly assigned to one of three concentrations of contrast agent in a 1:1:1 ratio based on each trial site. We use concealed allocation and an adequate computer-generated allocation sequence to avoid selection bias. Thus, neither the patient nor the outcome assessor knows to which group the patient is allocated. Therefore, if unblinding is deemed necessary, any of the investigators, coordinators, or CT operators can provide the information of the contrast agent used. If the assessors of the outcome learn this information, they should report this on the corresponding case report form.

### Interventions

Three different concentrations of contrast agent are randomly assigned to patients undergoing CT coronary angiography. A high tube potential is used for CT scans with the high-concentration contrast agent (370 mgI/ml), whereas a tube potential that is 20 kVp lower is used with the low-concentration contrast agents (270 mgI/ml and 320 mgI/ml).

#### Preparation of patients

If participants do not have contraindications for the use of the nitroglycerine, they receive sublingual nitroglycerine before coronary CT angiography. If a participant’s heart rate is equal to or greater than 60 beats per min, a beta-blocker is administered. If > 50 % stenosis is apparent on the coronary CT angiography, participants will undergo stress perfusion CT. In these cases, nitroglycerine and beta-blockers are not used. Separate intravenous lines are secured for the injection of adenosine and contrast media.

#### Contrast agents

Three contrast agents with different iodine concentrations (Visipaque 270, iodixanol 270 mgI/ml; GE Healthcare, Giles St Chalfont, United Kingdom vs. Visipaque 320, iodixanol 320 mgI/ml; GE Healthcare, Giles St Chalfont, United Kingdom vs. Pamiray 370, iopamidol 370 mgI/ml; Dongkook Pharma, Seoul, Korea) will be compared in this study. The participants are randomly assigned to different contrast agents in the same proportions. All contrast agents will be maintained by the same storage process, based on hospital systems, as used in general CT examinations. Each contrast agent will be administered via the antecubital vein of patients in the same triphasic injection. In the first phase, a 50-ml bolus of contrast agent will be injected at 5 ml/s. Then, 50 ml of mixed saline with 30 ml iodine and 20 ml saline will be injected into patients at 5 ml/s, followed by 40 ml of saline chaser. The total injected volume of the contrast agent is 80 ml.

#### Coronary CT protocol

All coronary CTA studies are acquired with a multidetector CT scanner (Discovery HD 750; Gemstone Spectral Imaging, GE Healthcare, Milwaukee, WI, USA). During scanning, participants hold their breath and are still. To obtain better image quality for each contrast agent, scans are performed with different protocols depending on whether high- or low- concentration contrast agents are used. If a high-concentration contrast agent (iopamidol 370 mgI/ml) is used, scans are conducted at 120 kVp for higher BMI (27 < BMI < 35) patients and at 100 kVp for lower BMI (15 < BMI ≤ 27) patients, with adjusted mAs (BMI-based tube potential selection). If a low-concentration contrast agent (iodixanol 270 mgI/ml or iodixanol 320 mgI/ml) is used, scans are conducted 20 kVp lower than in the BMI-based tube potential protocol: that is, at 100 kVp for higher BMI and 80 kVp for lower BMI. A beta-blocker is used for patients with a heart rate higher than 60 beats per minute. Scans initiate a bolus tracking method with a 4.8-s delay after reaching 100 Hounsfield units (HU) in the ascending aorta enhancement.

#### Myocardial perfusion CT

Stress myocardial perfusion CT will be performed in patients with at least one segment of greater than 50 % stenosis on coronary CT angiography. A static CT perfusion protocol will be used, and stress will be induced by infusing 140 mcg/kg/min adenosine under ECG monitoring for up to 6 min. The randomly assigned contrast agent, which was used for coronary CT angiography in the patient, will be injected 4 min 30 s after the adenosine injection, using the same injection method for contrast agent and image acquisition settings as used for the coronary CT angiography with the only difference being an additional scan delay of 2 s.

#### Image reconstruction

All images will be reconstructed using an iterative reconstruction algorithm at 50 % adaptive statistical iterative reconstruction (ASIR, GE Healthcare, Waukesha, Wis, USA).

#### Evaluation of radiation dose

The dose-length product (DLP) from each shooting will be collected. The effective radiation dose (mSv) will be calculated using a conversion factor of 0.014 mSv mGy^-1^ cm^-1^.

#### Retention

This study does not follow the participants’ outcome. Therefore, no specific plan has been developed to promote participant retention.

### Efficacy analysis

#### Primary efficacy analysis

The primary efficacy measurement is the HU value of the coronary arterial lumen acquired from the comparison of the image quality from the three different protocols of contrast media in coronary CT angiography. The coronary artery is divided into 17 segments according to the modified American Heart Association (AHA) classification, and luminal enhancement is measured for each segment with avoidance of the borderline between the lumen and the vessel wall or epicardial tissue, artifacts, or calcification. Measurement is performed on three different points in each segment and the average value is used for the HU value of each segment. The mean HU value of left main artery and proximal right coronary artery will be compared between the different arms of the trial.

